The primary Option B+ effectiveness outcome will be maternal retention in care at 6 months post ART initiation. Secondary outcomes will be earlier points along the Option B+ cascade, including facility delivery, maternal adherence to ART as assessed by medication possession ratio (calculated as the total number of day’s supply of ART received divided by the number of days of medicine required) > 90% at 3 and 6 months, viral suppression within 1 month of delivery, and mother-to-child HIV transmission by 6 months postpartum. Individual-level outcomes will only be assessed through 6 months post ART initiation to capture improvements within each step of the trial; however, in the case of mother-to-child HIV transmission, we will also quantify 18-month transmission rates to provide a broader picture of Option B+ effectiveness (these estimates will not be used in assessing SAIA-SCALE impact). Outcome measures are binary, with each woman’s progression through a given step defined as successful or unsuccessful. Progression through earlier steps will not be a prerequisite; women will remain eligible to complete later steps in the cascade despite failing to complete earlier steps.

##### Data sources

Service registries, located at each PMTCT service location (antenatal care, maternity, postpartum care, and at-risk child care for HIV-exposed children), facilitate longitudinal tracking of PMTCT utilization and outcomes for woman-infant pairs. As part of routine care, each woman is assigned a unique identification number that links across service points and clinics, which will be used to abstract registry data for study outcome measures. Retrospective individual-level data for the year prior to the implementation wave will be abstracted in the months following the end of each intervention wave (or in the months prior to wave I to collect baseline data). Ministry of Health administrative data will be used to estimate SAIA-SCALE’s reach across the provincial network of public sector health facilities. Administrative data, together with available community survey data (e.g., the Demographic and Health Surveys) will be used to estimate the number of woman-infant pairs who do not attend antenatal or maternity services.

##### Laboratory measures

Maternal blood samples are drawn at facilities and sent to a central laboratory in the Manica provincial capital for assessment of viral suppression. Results are reported back to facilities in copies/mL and recorded in registries as “detectable/not detectable.” Infant HIV testing is performed using polymerase chain reaction assessment of dried blood spots, analyzed at the provincial laboratory.

##### Power and sample size

We estimate a minimum of 40 Option B+ eligible women will present for a first antenatal care visit each month in each district across the three intervention facilities. For the primary individual-level outcome of 6-month retention in care, with 12 districts in three implementation periods, and assuming an intracluster correlation of 0.2 and α = 0.05, we will have 80% power to detect an increase in retention estimates from 17 to 25%. For the primary facility-level process outcome (infant diagnosis by eight weeks of age among exposed infants), we estimate baseline screening at 42% across the 36 study facilities. Using three, 1-year implementation periods, and targeting 12 districts with three facilities per district, and assuming a mean coverage in control periods of 42%, an intracluster correlation of 0.2 and α = 0.05, we will have 80% power to detect an increase to 78%.

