### Study setting, eligibility criteria, and randomization

#### Study setting

Manica province, located in central Mozambique with an estimated population of 2 million, includes 12 districts and 118 health facilities (Table 3). Utilization of public sector primary care services is high, with over 92% of women attending at least one antenatal care visit in the previous pregnancy, and 70% delivering in a health facility [26]. In central Mozambique, over 98% of utilization of formal health services is estimated to be in the public sector [27].

**Table 3 Tab3:** Population, health facility network, and utilization patterns by district in Manica province

District	Pop (2017)^a^	MOH clinics	Clinics with Option B+		1st ANC visits^b^	HIV+ in ANC^b^
	*N*	*N*	*N*	(%)	*N*	%
Barue	185,179	14	7	(50)	10,707	6.5%
Chimoio City	372,821	7	7	(100)	23,543	13.8%
Gondola	201,735	8	5	(63)	16,842	9.3%
Guro	96,930	11	7	(64)	5599	6.0%
Macate	85,062	6	3	(50)	5625	8.6%
Machaze	129,099	11	7	(64)	6813	11.9%
Macossa	48,648	5	3	(60)	2159	5.1%
Manica	225,000	17	11	(65)	13,583	11.8%
Mossurize	219,551	11	9	(82)	13,716	7.5%
Sussundenga	168,200	13	7	(54)	11,448	7.8%
Tambara	54,948	7	4	(57)	4399	5.4%
Vanduzi	124,064	8	3	(38)	5821	10.9%
Total	1,911,237	118	73	(62)	120,255	9.2%

^a^Estimates from 2017 census

^b^2015 annual estimates from routine health management information system

Manica has high HIV prevalence in adults (13.5% compared with 13.2% nationally) [26]. Though all facilities offer HIV testing in antenatal care and provision of antiretroviral medicines to prevent mother-to-child HIV transmission, Option B+ has targeted facilities with higher patient volume and larger capacity, and covers over 60% of facilities in the province.

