#### Eligibility criteria

All 12 districts in Manica province are included in SAIA-SCALE (Fig. 3). In each district, public sector health facilities with Option B+ services were ranked according to patient volume (number of first antenatal care visits in the year prior to randomization), and the highest 3 were purposively selected for study inclusion. This aligns with the Option B+ roll-out to the largest volume facilities with higher burden of HIV.

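### The stated minimum of 40 eligible women per month in each district is contradicted by Table 3 for three of 12 districts, and its monthly unit does not match the 80% power stated beside it

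*Protocol article*

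**What the plan says.** The section on power and sample size opens with its only patient volume: "We estimate a minimum of 40 Option B+ eligible women will present for a first antenatal care visit each month in each district". The count is taken over that district's three study facilities. The section then states 80% power for a rise in 6-month retention from 17% to 25%, with 12 districts, three implementation periods, an intracluster correlation of 0.2 and α = 0.05.

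The eligibility section ranks each district's Option B+ facilities by first antenatal visits, and "the highest 3 were purposively selected for study inclusion". The study facilities are therefore a subset of the district's facilities.

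Table 3, under Study setting, lists first antenatal visits and the percentage HIV-positive in antenatal care for each district. Its footnote describes both columns as "2015 annual estimates from routine health management information system". The text below the table says that all facilities offer HIV testing in antenatal care.

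**The concern.** The sentence sets a floor that every district must meet, and Table 3 lets the reader test it. A district total is an upper bound on what three of its facilities can see. If the total is below 40, the floor fails however concentrated attendance is.

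The figure is the only number of women given for the power calculation, so a reader checking the 80% has nothing else to use. If the figure is wrong for some districts, or carries the wrong time unit, the calculation cannot be verified as written.

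**Working it through.** **1. Reproducing the stated power.** The model is a stepped-wedge generalised least squares (Hussey–Hughes) calculation with:
- 12 district clusters, four per wave, and four yearly periods (one pre-intervention year plus three, as in the data analysis section);
- retention of 17% against 25%, ICC 0.2, and α = 0.05 taken as two-sided;
- total variance 0.17 × 0.83 = 0.1411, split into 0.2 × 0.1411 between districts and 0.8 × 0.1411 within districts, with a constant district effect and no separate facility level.

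Power is Φ(0.08/SE − 1.96).

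| Women per district per yearly period | SE | Power |
|---|---|---|
| 40 | 0.0289 | 79.1% |
| 480 (= 40 × 12) | 0.0084 | above 99.9% |

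The stated 80% is reproduced to within a point with 40 per yearly period. It is not reproduced with 40 per month. The same model with three facilities per district-period gives 79.0% for the process outcome (42% to 78%), which suggests that this is the kind of calculation used. Other variance conventions with 40 per period give 69.8% (within-cluster variance set to 0.1411) and 72.4% (variance at the mean proportion). None of them moves the match to 480.

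**2. Testing the minimum against Table 3.** Monthly HIV-positive first visits = annual first visits × HIV-positive share ÷ 12, over all facilities in the district. The table rows for the four lowest districts are "Macossa 48,648 5 3 (60) 2159 5.1", "Tambara 54,948 7 4 (57) 4399 5.4", "Guro 96,930 11 7 (64) 5599 6.0" and "Macate 85,062 6 3 (50) 5625 8.6"; the last two entries in each are first visits and percent positive.

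| District | Calculation | Per month | Range from rounding of the % |
|---|---|---|---|
| Macossa | 2159 × 0.051 / 12 | 9.2 | 9.1–9.3 |
| Tambara | 4399 × 0.054 / 12 | 19.8 | 19.6–20.0 |
| Guro | 5599 × 0.060 / 12 | 28.0 | 27.8–28.2 |
| Macate | 5625 × 0.086 / 12 | 40.3 | – |

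The other eight run from 52.9 (Vanduzi) to 270.7 (Chimoio City). The mean over the 12 districts is 80.9, so 40 could hold as an average but not as a minimum in each district.

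**3. What it would take to reach 40.** The HIV-positive share would have to be 40 × 12 / visits: 22.2% in Macossa, 10.9% in Tambara and 8.6% in Guro, against printed values of 5.1%, 5.4% and 6.0%. At the printed shares, first visits would have to be 4.4, 2.0 and 1.4 times those of 2015.

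**4. Does correcting the sizes change power?** The yearly Table 3 volumes replaced 480 in the same model, over random wave allocations because the drawn one is not given. The cluster autocorrelations below 1 are assumptions; the article gives none.

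| Cluster autocorrelation | 480 per district per year | Table 3 volumes (median) | 60% of Table 3 volumes (assumed share) |
|---|---|---|---|
| 1 (constant district effect) | above 99% | above 99% | above 99% |
| 0.95 | 95.1% | 95.3% | 93.9% |
| 0.90 | 75.9% | 76.0% | 74.2% |

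Replacing the minimum with the table's volumes leaves power essentially where it was.

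**The case against.** **Table 3 is an imperfect comparator.** Its counts are from 2015, whereas facilities were ranked on the year before an October 2017 randomization. The article does not say whether the HIV-positive share includes women already known positive or on treatment, who are eligible. The district rows give a weighted share of 9.7% (11,648 / 120,255) against a printed total of 9.2%. This makes Guro the most arguable of the three, since it needs 8.6% against 6.0%. It does not rescue Macossa, which would need more than four times its 2015 number, and it is unlikely to rescue Tambara, which would need twice its number. No growth of this size is documented. Women identified at delivery or while breastfeeding are also eligible, but the planning sentence counts first antenatal visits only.

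**The trial may lose nothing.** This stands. A reader might infer that the false minimum leaves the trial underpowered, and step 4 shows no such loss. Putting the monthly Table 3 counts, capped at 40, in as the size per yearly period gives about 73%, but that mixes a monthly count with a yearly period. On the reading that reproduces 80%, even Macossa, with about 110 women a year district-wide, exceeds 40 as long as its study facilities see at least 36% of them (40 / 110).

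**Other tempting readings are not supported.**
- That the plan assumes districts of equal size: a minimum allows any variation above it, and no such premise is stated.
- That Macate also fails: its total is 40.3, and all three of its Option B+ clinics are study facilities. Clinics without Option B+ also test antenatal women, so its margin is thin, but a shortfall is not shown.
- That the error makes a few large districts dominate the result: this follows from including all eligible women in all 12 districts and would remain if the sentence were corrected.

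**Conclusion.** The concern holds as a wrong and unclear planning input. On the article's own 2015 data the stated minimum is false for three of 12 districts, which reach at most 23%, 50% and 70% of it (9.2/40, 19.8/40, 28.0/40). These are upper bounds, because they assume that every HIV-positive antenatal woman in the district attends a study facility. Separately, 40 per month does not fit the 80% beside it, whereas 40 per yearly period does.

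The second point rests on the model in step 1, which the article does not name; the authors may have used another. The first needs no model and depends only on Table 3 being a fair guide to volume. Neither shows a loss of power or a flaw in the design, the choice of districts or the analysis. The correction should be made because the power statement cannot be checked as it stands.

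**What to change.** In the power and sample size section:
1. Replace the common minimum with the expected number of eligible women in each district's three selected facilities, starting from the first-visit counts already used to rank them.
2. State whether 40 is per month or per analysis period.
3. Restate the power, or the detectable difference, with these unequal district sizes under the wave allocation already drawn.

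The cost is a text correction and one recalculation from facility counts already used for the ranking. Districts, facilities and trial conduct do not change.

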##### Data analysis

Facility-level outcome data will be analyzed using linear mixed-effects models, with clustering by district and an exchangeable correlation matrix. Data for each facility will be aggregated at 2-month intervals for the entire study period, from 1 year pre-intervention through the third year of the intervention. In the primary analysis, facilities will be considered unexposed prior to the introduction of SAIA-Scale and exposed thereafter, and models will be adjusted for study time.

Individual-level outcomes will be analyzed using generalized linear mixed-effects models, with two levels of clustering by facility and district. Individuals’ exposure status will depend on their facilities’ exposure status at the time of their first visit, and models will be adjusted for study time.

For both facility-level and individual-level outcomes, primary analyses will exclude data from the roll-out phase in each district and will consider the intervention effect to be fixed throughout the exposed period. Sensitivity analyses will (a) test for increasing or decreasing effect of the intervention over time and (b) compare the effect of the intervention during the intensive and maintenance phases using interaction terms between exposure status and calendar time or study phase. Effect modification of the intervention effect by facility-level factors such as patient volume, provider training, and distance from the district office will be assessed using interaction terms, with potential effect modifiers assessed categorically or as binary variables depending on distribution. Potential adjustment variables to be assessed include calendar year and individual-level factors such as gestational age at entry into care and timing of HIV diagnosis (during or prior to current pregnancy).

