**Methods:**

The SAIA-SCALE stepped wedge trial includes three implementation waves, each 12 months in duration. Districts are the unit of assignment, with four districts randomly assigned per wave, covering all 12 districts in Manica province, Mozambique. In each district, the three highest volume health facilities will receive the SAIA-SCALE intervention (totaling 36 intervention facilities). The RE-AIM framework will guide SAIA-SCALE’s evaluation. Reach describes the proportion of clinics and population in Manica province reached, and sub-groups not reached. Effectiveness assesses impact on PMTCT process measures and patient-level outcomes. Adoption describes the proportion of districts/clinics adopting SAIA-SCALE, and determinants of adoption using the Organizational Readiness for Implementing Change (ORIC) tool. Implementation will identify SAIA-SCALE core elements and determinants of successful implementation using the Consolidated Framework for Implementation Research (CFIR). Maintenance describes the proportion of districts sustaining the intervention. We will also estimate the budget and program impact from the payer perspective for national scale-up.

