#### Randomization

Districts were randomized without restriction into implementation waves during a meeting with provincial health authorities and study leadership in Manica province in October, 2017. Districts were randomized prior to selection of intervention facilities. Though already allocated, second and third wave districts have not been informed of the implementation timeframe for their district.

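### The model for facility process outcomes omits the facility level and fixes a time-constant correlation, and neither primary model names district-by-period variation, so the 5% error rate depends on an unstated assumption

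*Protocol article*

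**What the plan says.** The Data analysis section of the protocol article gives one covariance structure for each outcome type.

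- **Facility process outcomes:** "Facility-level outcome data will be analyzed using linear mixed-effects models, with clustering by district and an exchangeable correlation matrix". The records are defined by: "Data for each facility will be aggregated at 2-month intervals for the entire study period". That period runs from one year before the intervention to the end of its third year, so each of the 36 facilities has up to 4 × 6 = 24 records. The roll-out interval is then dropped ("primary analyses will exclude data from the roll-out phase in each district").
- **Individual outcomes, including retention:** "generalized linear mixed-effects models, with two levels of clustering by facility and district".

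Both models adjust for study time. The listed sensitivity analyses let the intervention effect change over time or differ by phase; none changes the correlation structure.

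On the design, the abstract states: "Districts are the unit of assignment, with four districts randomly assigned per wave". The Randomization section adds: "Districts were randomized without restriction into implementation waves". Power and sample size uses a single ICC of 0.2, "with 12 districts in three implementation periods", with no separate value for records from different periods.

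**The concern.** Three features of the design meet here.

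1. Stable differences between the three facilities of a district have no place in the process-outcome model other than the residual. The next paragraph of the same section does name the facility level for individual outcomes, so the section is not consistent with itself.
2. An exchangeable matrix gives two records 2 months apart the same correlation as two records almost four years apart. The individual model, with only facility and district intercepts, implies the same constancy.
3. All three study facilities in a district become exposed at the district's start. A change specific to one district in one year is therefore shared by all its records for that year and is partly aligned with exposure. Adjustment for study time removes only changes common to all districts.

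The protocol itself gives reasons to expect district-specific change. It plans for turnover of district managers (Process for introducing SAIA), cites unreliable medicine and supply systems (Background), and says that district management shapes the environment in its facilities (Goals and objectives). At stake is the false-positive rate for 6-month retention, the primary effectiveness outcome, and the precision reported for the process outcomes.

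**Working it through.** **Inputs from the protocol.** 12 districts, 4 per wave, 3 waves; 4 yearly periods (baseline plus three); 3 facilities per district; at least 40 women per district per month, so 480 per year; ICC 0.2; alpha 0.05 (two-sided assumed); control rates 17% (retention) and 42% (infant diagnosis).

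**Assumed, because the documents give no value.** The ratio of between-year to within-year correlation in a district (autocorrelation c), and the facility variance.

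**Step 1: the plan's own power.** The standard stepped-wedge variance with time-constant correlation is

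Var = Iσ²(σ² + Tτ²) / [(IU − W)σ² + (U² + ITU − TW − IV)τ²],

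where τ² is the district variance and σ² the sampling variance of a district-period mean. With I = 12, T = 4, U = 24, W = 224 and V = 56, the bracket is 64σ² + 160τ².

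- Retention: total variance 0.17 × 0.83 = 0.1411, τ² = 0.02822. With 40 women per district-period, σ² = 0.11288/40 = 0.002822, SE = 0.0289 and power = Φ(0.08/0.0289 − 1.96) = 79%.
- Infant diagnosis: τ² = 0.04872. With three facility observations per district-period, σ² = 0.19488/3 = 0.06496, SE = 0.130 and power = Φ(0.36/0.130 − 1.96) = 79%.

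Both stated 80% figures are reproduced to within about 1 point, and both assume c = 1. The retention figure is reproduced with 40 women per district-period, although the protocol gives 40 as a monthly number.

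**Step 2: retention under decay (linear approximation).** With 480 women, σ² = 0.11288/480 = 0.000235 and the model SE is 0.0084. If a share 1 − c of the district variance is year-specific, each district-year mean gains variance (1 − c) × 0.02822. At c = 0.99 that is 0.000282, already more than the sampling variance. The true SE of the planned estimator follows from the sandwich formula, and type I error = 2Φ(−1.96 × model SE / true SE).

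| c (ICC 0.2) | True SE | True/model SE | Type I error |
|---|---|---|---|
| 1 | 0.0084 | 1.00 | 5% |
| 0.99 | 0.0124 | 1.48 | 19% |
| 0.95 | 0.0222 | 2.64 | 46% |
| 0.90 | 0.0302 | 3.60 | 59% |
| 0.80 | 0.0419 | 5.00 | 69% |

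At c = 0.95 and 0.80, type I error is 19% and 42% with ICC 0.05, and 8% and 16% with ICC 0.01. A logistic simulation at ICC 0.2 (800 null trials per setting) gave 5.5% at c = 1 and 35%, 47% and 58% at 0.95, 0.90 and 0.80.

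**Step 3: process outcomes, facility level omitted, no district-by-period variation.** With three facilities per district, about two thirds of the facility variance falls into the residual. The SE is inflated by roughly √(1 + 2r/3), where r is facility variance over residual variance: √1.333 = 1.155 at r = 0.5 and √2.333 = 1.53 at r = 2. The full matrix calculation gives 1.15 to 1.52. With facility variance at 10%, 20% and 40% of the total, type I error is 4.2%, 3.1% and 1.2%.

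**Step 4: process outcomes with district-by-year variation.**

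- No facility variance, district-by-year variance 1%, 2% and 4% of the total: 7.2%, 9.4% and 13.5%.
- Facility variance 20%, same district-by-year values: 5.3%, 7.7% and 12.3%. The two gaps partly offset.
- In the last case, adding only a facility intercept raises 12.3% to 16.1%, because it removes the conservative part and leaves the other.

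**Step 5: allocations.** 12!/(4!)³ = 34,650.

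**The case against.** The strongest reply is that the size rests on quantities the protocol does not give. With constant district correlation, the retention model keeps its 5%. A reader might infer that the standard errors are wrong outright and that neither primary p-value can be trusted. The documents do not support that: they give no autocorrelation and no facility variance, and for process outcomes the two omissions pull in opposite directions and can nearly cancel (5.3% in one case above).

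Other points on that side:

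- *This is a condensed article.* A district-by-period term in the individual model, and small-sample inference for 12 districts, may be in an analysis plan not shown. That is fair for those two items. It does not cover the process-outcome model, where district clustering and the exchangeable matrix are stated choices.
- *The exchangeable matrix might mean exchangeable within facility*, which would act as a facility intercept. This is possible, but the sentence says district, and it would still fix a constant correlation over time.
- *Equal clusters of 480 are a simplification.* In Table 3, first antenatal visits times HIV prevalence give about 110 women a year in Macossa (2159 × 5.1%) and 238 in Tambara (4399 × 5.4%), over all facilities. Other districts are larger, so the net effect is unclear. The retention percentages are a sensitivity range, not a forecast.
- *Linear and logistic results differ* by about 11 points, with the same conclusion.

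It may also be tempting to ask for a binomial model on the ground that facility proportions are unweighted. The protocol never says they are, so that does not follow.

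**Conclusion.** The point stands in conditional form. As written, the process-outcome model lacks the facility level that the neighbouring paragraph includes and holds correlation constant over four years. Neither model names district-by-period variation, and no listed sensitivity analysis would reveal the problem.

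For process outcomes the direction depends on which variance dominates: conservative from the missing facility level, anti-conservative from the missing district-by-period variation. For retention the risk is one-directional and sensitive. At the protocol's own ICC, type I error stays at 5% only if year-specific district variance is essentially nil; 1% of the district variance takes it to about 19%. At ICC 0.01 the range is milder, about 8% to 16%. These figures assume equal district-years of 480 women, yearly periods and a normal reference distribution.

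**What to change.** For both outcome types, specify random intercepts for district and for facility within district, plus a district-by-period random effect with the period length stated (or a correlation that decays with time apart). Make these changes together; adding the facility level alone can worsen inflation.

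Confirm the primary tests with a permutation test over the 34,650 allocations of 12 districts to three waves of four. Unrestricted randomization makes this valid, and under the null of no effect it does not rely on the assumed variance structure. For the linear models, a small-sample correction is an alternative alongside the added term, but not a substitute for it: in a simulation of the district-only facility model with 4% district-by-year variance, a t reference with 10 degrees of freedom lowered the error only from 11.8% to 8.6%.

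The cost is a few sentences, some computing and wider retention intervals. With the district-by-period term and 480 women per district-year, power for 17% to 25% is about 95%, 76% and 49% at autocorrelation 0.95, 0.90 and 0.80. With 40 per district-period it is 62%, 51% and 37%, against 79% with no decay.

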SAIA-SCALE employs a stepped wedge cluster randomized trial implementation schedule to randomly allocate all 12 districts in Manica province into three implementation waves, staggered by 1 year (3 years total). District maternal and child health supervisors deliver the intervention in three health facilities per district (36 total) during a 1-year intensive phase (mentored by research nurses experienced with the intervention from the SAIA trial), with subsequent implementation led independently by the district supervisors (sustainment phase) (Fig. 1). Our design has a number of advantages for this study. First, a phased-in design will ensure that all 12 districts in Manica province will receive the evidence-based SAIA implementation strategy. Second, the design will assess SAIA’s performance under pragmatic conditions. Third, a randomized design reduces potential confounding, and provides robust evidence of SAIA-SCALE’s impact. Fourth, the design is appropriate to assess the dissemination strategy for SAIA-SCALE (delivery by district health system managers), while assessing impact on the facility and patient levels. Finally, the design allows for assessing maturation patterns in SAIA-SCALE’s effects over time, including during the intensive and sustainment phases.

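### Patient volume and distance from the district office are to be tested as effect modifiers only in grouped form, which loses information if the gradient is smooth

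*Protocol article*

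**What the plan says.** The Data analysis section of the protocol article plans to examine "Effect modification of the intervention effect by facility-level factors such as patient volume, provider training, and distance from the district office" by interaction terms, and fixes their form: "with potential effect modifiers assessed categorically or as binary variables depending on distribution". It gives neither the number of groups nor the cut-points, and it mentions no continuous analysis.

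The Eligibility criteria section defines "patient volume (number of first antenatal care visits in the year prior to randomization") as the basis for ranking facilities, so volume is already held as a count. Distance is continuous by nature. The scale of provider training is not stated, and it may well be categorical.

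The units available are set under Goals and objectives: "District maternal and child health supervisors deliver the intervention in three health facilities per district (36 total"), with a schedule to "randomly allocate all 12 districts in Manica province into three implementation waves, staggered by 1 year".

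The Power and sample size section covers two main effects only. For retention it reads "assuming an intracluster correlation of 0.2 and α = 0.05, we will have 80% power to detect an increase in retention estimates from 17 to 25"%, and for infant diagnosis "an intracluster correlation of 0.2 and α = 0.05, we will have 80% power to detect an increase to 78"%. It gives no power for any interaction.

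**The concern.** Grouping a continuous modifier treats all facilities in a group as alike and those just either side of a cut as different. If the effect of SAIA-SCALE rises or falls smoothly with volume or distance, part of the information about that gradient is discarded. Only 36 facilities in 12 districts carry these interactions, so there is little to spare. A real gradient becomes easier to miss, and the answer partly depends on where the cuts fall. Choosing the form from the observed distribution does not avoid this, because every form the sentence allows is a grouped one.

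This is a method the protocol states, not a detail left open. A separate analysis plan could set the cut-points, but if it followed this sentence it would still group.

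At stake is what the trial can say about the kind of facility in which the strategy works better or worse. The primary comparisons are not at stake.

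**Working it through.** **Inputs from the protocol.** 36 facilities, three in each of 12 districts (Goals and objectives); α = 0.05 (Power and sample size), taken here as two-sided; modifiers grouped, with cuts unspecified (Data analysis). The protocol has no figure for these interactions to reproduce.

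**Assumptions.** The modification is linear in the modifier. The modifier is near-normal, possibly after a log transformation. The continuous 1-df test has 80% power, chosen only to show the size of the change. District clustering is not modelled, so the equivalent numbers of facilities are a guide.

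**Step 1: information kept.** Under a linear gradient this is the squared correlation between the modifier and its grouped version. For a normal modifier cut in two at c, with share p above the cut, it is φ(c)² / [p(1−p)].

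- Median split: c = 0, p = 0.5, φ(0)² = 1/(2π) = 0.159; 0.159/0.25 = 2/π = 0.637.
- 25/75 cut: c = 0.674, φ(c) = 0.318; 0.318²/0.1875 = 0.539.
- 10/90 cut: c = 1.282, φ(c) = 0.1755; 0.1755²/0.09 = 0.342.

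For equal-sized groups of a normal modifier:

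| Groups | Kept | Lost | 36 facilities act like |
|---|---|---|---|
| 2 | 0.637 | 36% | 36 × 0.637 ≈ 23 |
| 3 | 0.793 | 21% | 36 × 0.793 ≈ 29 |
| 4 | 0.861 | 14% | 36 × 0.861 ≈ 31 |

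In simulated sets of 36 facilities, a median split keeps 64% on average (5th to 95th percentile 55% to 73%).

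**Step 2: other shapes.** Losses with 2, 3, 4 and 5 equal groups, by simulation, with the effect linear on the scale shown:

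| Modifier | 2 | 3 | 4 | 5 |
|---|---|---|---|---|
| Uniform | 25% | 11% | 6% | 4% |
| Exponential, raw scale | 52% | 35% | 27% | 21% |
| Lognormal (log SD 1), raw scale | 73% | 60% | 52% | 47% |

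**Step 3: power.** The continuous test with 80% power has a standardised effect of 1.960 + 0.842 = 2.802, or a noncentrality of 2.802² = 7.85.

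- Median split, 1 df: Φ(2.802 × √0.637 − 1.960) = Φ(0.28) = 0.61.
- Tertiles, 2 df: noncentrality 7.85 × 0.793 = 6.22; critical value 5.99; power 0.60.
- Quartiles, 3 df: noncentrality 7.85 × 0.861 = 6.76; critical value 7.81; power 0.57.
- Tertiles scored as a trend, 1 df: Φ(2.802 × √0.793 − 1.960) = 0.70, but the protocol does not specify a trend score.

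More groups keep more information, but an ordinary categorical interaction spends it on extra degrees of freedom. All three such forms therefore end at about 57% to 61%.

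**Step 4: the alternative.** If linear and quadratic terms are tested jointly (2 df) when the truth is linear, the noncentrality stays at 7.85 and power is 0.71. The 1-df linear test keeps the assumed 0.80.

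**The case against.** A reader might infer that the plan discards about a third of the information. The protocol does not support that as a general statement. It is the result for a median split of a near-normal modifier with a linear effect, and the protocol commits to none of these. Across the cases above the loss runs from 4% to 73%, and with a threshold at the cut it is nil.

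A reader might also apply Table 3 to this question. A median split of its district totals of first antenatal visits loses 26% on the log scale. But those are 12 district totals over all clinics, not the volumes of the 36 selected facilities, and nothing is given for distance. They cannot size the loss in the planned analysis.

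The 80% starting power is assumed. If the continuous test had only 20%, a median split would leave about 14%: a small absolute loss in a test that is uninformative either way.

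It is tempting to say that the national scale-up scenarios depend on these results. The economic evaluation section lists facility characteristics as one dimension of the scenarios, but it does not tie them to these interactions.

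The continuous form has costs too. Skewed modifiers can give a few facilities high leverage, and a joint test with curvature (71%) is hardly better than a tertile trend (70%). That is a reason to make the 1-df linear term the main test and to check influence, not a reason to group. Exact cut-points may properly be left to an analysis plan.

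What stands is that the protocol rules in only grouped forms for modifiers that could be analysed on their own scale.

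**Conclusion.** The point holds in a limited form, as a minor improvement to a secondary analysis. For a near-normal modifier with a roughly linear effect, the planned grouping loses about 14% to 36% of the information with four to two equal groups. The loss is larger for off-centre cuts (46% at 25/75, 66% at 10/90) and for skewed modifiers with a raw-scale gradient. Against an assumed 80% on the continuous scale, the ordinary binary and categorical tests have about 57% to 61%. These figures rest on a smooth gradient and an assumed baseline power; if the true change is a threshold at the cut, they do not apply. No primary estimate, error rate or stated power changes.

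**What to change.** In the Data analysis section, state the following:

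- Patient volume (log scale if skewed) and distance from the district office enter the exposure interaction as continuous terms, with the 1-df linear interaction as the main test.
- Curvature (for example one quadratic term) and influential facilities are checked as a sensitivity analysis.
- Categories are used to display fitted effects, and for modifiers that are categorical by nature, such as provider training if it is recorded that way.

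The cost is a sentence or two of analysis wording and no new data. The small downside is an assumed linear or log-linear form and possible leverage from extreme facilities, which the sensitivity analysis addresses.
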